In the FFVM, patients are allowed to receive visits from one or two close family members for up to 12 consecutive hours each day. Family members who agree to join the family visits have to attend a structured meeting at the ICU in which they receive guidance about the ICU environment, common ICU treatments, rehabilitation and basic infection control practices, multidisciplinary work at the ICU, and information on palliative care and delirium prevention. Additionally, family members receive an information brochure and are encouraged to access a website, both of which are designed to explain what happens during and after an ICU stay to legitimize emotions and improve cooperation with relatives without increasing the ICU staff workload. In addition to family visitation, patients in the FFVM are allowed to receive social visits at specific time intervals (according to the local ICU policies) from friends or other family members who did not qualify for flexible family visitation. In the RFVM, patients are allowed visitors according to routine ICU practices, but limited to the maximum of 4.5 h of visitation per day. Visitors are not required to attend the structured meeting in the RFVM.

The study primary outcome is the cumulative incidence of delirium during the ICU stay measured by trained researchers using the Confusion Assessment Method for the ICU (CAM-ICU) [11]. Secondary outcomes include daily hazard of delirium, ventilator-free days at day 7, any ICU-acquired infections according to the Centers for Disease Control and Prevention (CDC) criteria [12–14], ICU length of stay, and hospital mortality among the patients; symptoms of anxiety and depression measured by the Hospital Anxiety and Depression Scale (HADS) [15] and satisfaction measured by the Critical Care Family Needs Inventory (CCFNI) [16] among the family members; and prevalence of burnout syndrome evaluated by the Maslach Burnout Inventory (MBI) [17] among the ICU professionals. Tertiary outcomes include need for antipsychotic agents, need for mechanical restraints, unplanned loss of invasive devices (venous catheter, enteral tube, or urinary catheter), coma-free days at day 7, and ICU-acquired pneumonia, urinary tract infection, or bloodstream infection among the patients; self-perception of involvement in patient care among the family members; and satisfaction among the ICU professionals.

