## Statistical analysis plan

### Overall principles

The main analysis for each outcome will be performed at the subject level using the intention-to-treat (ITT) principle, meaning that all participants with a recorded outcome will be included in the analysis and will be analyzed according to the treatment group to which they were randomized (FFVM or RFVM), independent of actual visiting hours. Moreover, all analyses will account for the cluster-randomized crossover design to ensure correct type I error rates and confidence intervals (CIs). A significance level of 0.05, adjusted for multiple comparisons when appropriate, will be used for all statistical comparisons. Analysis will start once all data to discharge for the last included patient have been obtained, the database has been cleaned and locked, and the SAP has been submitted for publication. The R Development Core Team software will be used for analysis [18].

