Self-perception of involvement in patient care					
Score:^e^ mean (SD)	xx.x (xx.x)	xx.x (xx.x)	MD	x.xx (x.xx-x.xx)*	x.xx
ICU professionals					
Satisfaction of ICU professionals with the ICU visiting policy score:^f^ mean (SD)	xx.x (xx.x)	xx.x (xx.x)	MD	x.xx (x.xx-x.xx)*	x.xx

*BSI* bloodstream infection, *CCFNI* Critical Care Family Needs Inventory, *CI* confidence interval, *FFVM* flexible family visitation model, *HADS* Hospital Anxiety and Depression Scale, *HR* hazard ratio, *ICU* intensive care unit, *MD* mean difference, *PR* prevalence ratio, *RFVM* restrictive family visitation model, *RR* risk ratio, *SD* standard deviation, *UTI* urinary tract infection

^a^Adjusted for multiple comparisons with Bonferroni correction when appropriate

^b^According to the Confusion Assessment Method for the Intensive Care Unit (CAM-ICU) criteria

^c^According to the Centers for Disease Control and Prevention (CDC) criteria

^d^Maslach Burnout Inventory (MBI) total score > − 9

^e^The self-perception of involvement in patient care score varies from 0 (no involvement) to 27 (maximum degree of involvement)

^f^The satisfaction of ICU professionals with the ICU visiting policy score varies from 0 (unsatisfied) to 4 (very satisfied)

^*^95% confidence interval

^**^99% confidence interval

^***^98.3% confidence interval

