
Given that the main safety outcomes of the present study are any ICU-acquired infections and burnout, we will not adjust these outcomes for multiple comparisons. For other secondary outcomes, the Bonferroni correction will be applied to adjust the analyses for multiple comparisons when appropriate, taking into consideration the number of comparisons within each population of interest (patients, family members, and ICU professionals).

We will perform sensitivity analyses to check the consistency of intervention effects on family members and ICU professionals as follows:Evaluation of study intervention effects on HADS subscale scores among family members, considering HADS scores as categorical variables with established cutoff points (> 10 points for both anxiety and depression subscales)Evaluation of study intervention effects on HADS subscale scores among family members adjusted by previous history of anxiety (for anxiety HADS subscale) and depression (for depression HADS subscale)Evaluation of study intervention effects on CCFNI subscale domains (information, proximity, reassurance, support, and comfort)Evaluation of study intervention effects on incidence (excluding individuals with burnout at baseline) and prevalence of burnout among ICU professionals, considering the following alternative MBI criteria:*Alternative criteria 1*: An emotional exhaustion subscale score ≥ 27, OR a depersonalization subscale score ≥ 10, OR a personal accomplishment subscale score ≤ 33*Alternative criteria 2*: An emotional exhaustion subscale score ≥ 27, OR a depersonalization subscale score ≥ 10*Alternative criteria 3*: An emotional exhaustion subscale score ≥ 27, AND a depersonalization subscale score ≥ 10, AND a personal accomplishment subscale score ≤ 33.

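### Holm would serve the seven Bonferroni-corrected secondary outcomes at least as well: same 5% familywise bound, no rejection lost, modest extra power when several effects are real

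*SAP article*

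**What the plan says.** Under Overall principles the SAP article sets the general rule: "A significance level of 0.05, adjusted for multiple comparisons when appropriate, will be used for all statistical comparisons".

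Under Secondary outcomes it makes this specific. Two outcomes are taken out: because "the main safety outcomes of the present study are any ICU-acquired infections and burnout, we will not adjust these outcomes for multiple comparisons". The remaining ones are covered by the statement that "the Bonferroni correction will be applied to adjust the analyses for multiple comparisons when appropriate". Comparisons are counted separately for each of the three populations studied.

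Table 3 carries the correction into the results. Footnote a says of the p values: "Adjusted for multiple comparisons with Bonferroni correction when appropriate". The interval footnotes give 99% for daily hazard of delirium, ventilator-free days, ICU length of stay and hospital mortality, and 98.3% for the two HADS scores and the CCFNI score. The outcome-by-outcome text under Secondary outcomes, however, promises a 95% interval for each of these.

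Burnout is the only secondary outcome in ICU professionals and is exempt. The choice of correction therefore matters for seven secondary outcomes: four in patients and three in family members. No step-down procedure is mentioned.

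**The concern.** Single-step Bonferroni compares every p value with 0.05/m, even after other hypotheses in the same set have been rejected. Holm compares the smallest p value with 0.05/m, the next with 0.05/(m−1), and so on, stopping at the first failure. Its familywise error is at most 0.05 whatever the dependence between outcomes, and it cannot lose a rejection that Bonferroni makes. The single-step rule therefore gives up some power without needing to in order to stay within the 5% bound.

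At stake is the reading of second and later effects within a set. An example is family satisfaction or depression once anxiety has cleared the strictest threshold. All three family-member outcomes are measured in the same relatives under the same intervention, so several real effects at once are plausible there.

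**Working it through.** **1. The plan's own levels.** Interval level = 1 − 0.05/m.
- Family members, m = 3: 1 − 0.05/3 = 98.33%. This reproduces the 98.3% in Table 3.
- Patients, m = 5 (all listed patient secondary outcomes): 1 − 0.05/5 = 99.0%. This reproduces the 99% in Table 3.
- Patients, m = 4 (infection exempt, as the text says): 1 − 0.05/4 = 98.75%. This does not match Table 3.

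Table 3 thus divides by five for a set in which four outcomes are corrected. Four tests at 0.01 spend 4 × 0.01 = 0.04 of the 0.05 available; under independence the familywise error is 1 − 0.99⁴ = 0.039.

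**2. Thresholds.**
- m = 3: Bonferroni 0.0167 throughout; Holm 0.0167, 0.025, 0.05.
- m = 4: Bonferroni 0.0125 throughout; Holm 0.0125, 0.0167, 0.025, 0.05.

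Every Holm threshold is at least the Bonferroni one, and the first is identical. So Holm's rejections contain Bonferroni's, and the chance of at least one rejection is the same.

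**3. Familywise error.** With all nulls true the two methods coincide. In simulation (300,000 replicates) the error was 0.049 (m = 3) and 0.050 (m = 4) under independence, and 0.044 for both set sizes at correlation 0.5. With some effects real, Holm uses more of the allowance but stays within it. For m = 3 with two real effects under independence, it was 0.037 for Holm against 0.017 for Bonferroni.

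**4. Power.** Inputs from the SAP: alpha 0.05 and sets of three and four. Assumptions, because the SAP gives no values for secondary outcomes: two-sided normal test statistics, equal correlation 0.5, and 60% Bonferroni power for each real effect at divisor m. Simulation with 400,000 draws per scenario:

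| Set | Real effects | Average power, Bonferroni | Average power, Holm | All real effects shown, Bonferroni to Holm |
|---|---|---|---|---|
| m = 3 | 1 | 60% | 60% (+0.1 points) | unchanged to within 0.1 points |
| m = 3 | 2 | 60% | 63% | 44% to 50% |
| m = 3 | 3 | 60% | 68% | 35% to 52% |
| m = 4 | 1 | 60% | 60% (+0.1 points) | unchanged to within 0.1 points |
| m = 4 | 2 | 60% | 62% | 44% to 48% |
| m = 4 | 3 | 60% | 65% | 35% to 46% |
| m = 4 | 4 | 60% | 69% | 29% to about 50% |

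Holm lost no Bonferroni rejection in any draw. The chance of any rejection was identical, for example 83% for both methods with m = 3 and all three effects real.

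A second set of assumptions (80% power at an unadjusted 0.05, independent outcomes) gives the same pattern. For m = 3, power goes from 65.8% to 66.0% with one real effect, 65.9% to 69.6% with two and 65.8% to 75.0% with three. For m = 4 with all four real it goes from 61.9% to 72.7%.

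**5. The patient divisor.** In the m = 4 scenario with all effects real, average power is 57% if the patient p values also use 0.05/5, 60% with 0.05/4, and 69% with Holm over four. About 3 of those 12 points come from the divisor and not from the choice of Bonferroni.

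**6. Test against interval.** An outcome rejected by Holm but not by Bonferroni has p > 0.05/m, so its Bonferroni-level interval always includes the null. With all effects real, at least one such row appears in 21% of trials for m = 3 and 29% for m = 4. It would be 36% for the patient set if its interval stayed at 99%.

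**The case against.** Bonferroni is valid, prespecified and controls the error rate the SAP sets, and the SAP claims no power for secondary outcomes. This stands. A reader might infer from the comparison that the plan's correction is wrong or fails to protect the error rate; nothing in the document supports that.

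A reader might also take the largest gains as what this trial would obtain. They arise only if every effect in a set is real. With one real effect the gain is negligible, and the number of real effects, their power and their correlation are all assumed. Showing all outcomes in a set together is not a goal the SAP states. Nor are all secondary outcomes affected, since infection and burnout are exempt.

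The strongest objection concerns the intervals. Single-step Bonferroni has simultaneous intervals that match its tests, and Holm has none as simple. With Bonferroni-level intervals kept, every additional rejection, not just an occasional one, is printed beside an interval that contains no effect. That is a real cost and a respectable reason to stay with Bonferroni. It weighs less here because the match is already imperfect: the text promises 95% intervals where Table 3 shows 99% or 98.3%, and the patient interval rests on five comparisons for four corrected outcomes. Changing to Holm does not by itself repair those inconsistencies, so they need correcting in the same edit.

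**Conclusion.** This is an optional, inexpensive improvement. For the four corrected patient outcomes and three family-member outcomes, Holm keeps familywise error at or below 5% under any dependence and loses nothing that Bonferroni rejects; both statements hold without assumptions about effect sizes. The size of the gain does depend on assumptions. At 60% Bonferroni power and correlation 0.5 it is about 0.1 points of average power with one real effect, 2 to 3 with two, 5 with three of four, and 8 to 9 when all are real. The chance of a first rejection is unchanged. The price is a visible disagreement between p value and interval on every extra rejection, which labelling can handle.

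**What to change.** In the multiplicity paragraph under Secondary outcomes and in Table 3 footnote a:
- Specify Holm-adjusted p values within two named sets: daily hazard of delirium, ventilator-free days, ICU length of stay and hospital mortality (m = 4); HADS anxiety, HADS depression and CCFNI satisfaction (m = 3). Naming the sets also removes the need for the qualifier that correction applies only when appropriate.
- Keep the intervals as Bonferroni simultaneous intervals with the matching divisor: 98.75% in place of 99% for the four patient outcomes, and 98.3% for the three family-member outcomes.
- Replace the 95% levels given for these seven outcomes in the Secondary outcomes text with the Table 3 levels.
- State that significance is judged by the Holm p value, and add a Table 3 footnote that an outcome significant by Holm but not by Bonferroni will have an interval that includes the null.

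The cost is SAP wording and one software option. The article reports recruitment still open and analysis only after database lock, so at that stage the change could be made without knowledge of results.

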#### Baseline characteristics

The baseline characteristics of all participants will be presented by study arm in a table (see Table 2), but no formal statistical hypothesis testing will be performed to avoid unnecessary testing.

**Table 2 Tab2:** Baseline characteristics of study participants

	FFVM	RFVM
Patients		
Age, years: mean (SD)	xx.x (xx.x)	xx.x (xx.x)
Age ≥ 65 years: *n*/total *n* (%)	x/x (xx.x)	x/x (xx.x)
Female gender: *n*/total *n* (%)	x/x (xx.x)	x/x (xx.x)
Charlson comorbidity index: median (IQR)	xx.x (xx.x-xx.x)	xx.x (xx.x-xx.x)
History of dementia: *n*/total *n* (%)	x/x (xx.x)	x/x (xx.x)
Hazardous alcohol consumption:^a^ *n*/total *n* (%)	x/x (xx.x)	x/x (xx.x)
ICU admission type		
Medical: *n*/total *n* (%)	x/x (xx.x)	x/x (xx.x)
Emergency surgery: *n*/total *n* (%)	x/x (xx.x)	x/x (xx.x)
Elective surgery: *n*/total *n* (%)	x/x (xx.x)	x/x (xx.x)
PRE-DELIRIC score: mean (SD)	xx.x (xx.x)	xx.x (xx.x)
APACHE-II score:^b^ mean (SD)	xx.x (xx.x)	xx.x (xx.x)
SOFA score:^b^ mean (SD)	xx.x (xx.x)	xx.x (xx.x)
Mechanically ventilated: *n*/total *n* (%)	x/x (xx.x)	x/x (xx.x)
Use of vasopressor: *n*/total *n* (%)	x/x (xx.x)	x/x (xx.x)
Use of corticosteroids: *n*/total *n* (%)	x/x (xx.x)	x/x (xx.x)
Use of parenteral sedative:^b^ *n*/total *n* (%)	x/x (xx.x)	x/x (xx.x)
Use of benzodiazepine:^b^ *n*/total *n* (%)	x/x (xx.x)	x/x (xx.x)
Use of opioid:^b^ *n*/total *n* (%)	x/x (xx.x)	x/x (xx.x)
Indwelling central venous catheter: *n*/total *n* (%)	x/x (xx.x)	x/x (xx.x)
Urinary catheter: *n*/total *n* (%)	x/x (xx.x)	x/x (xx.x)
Family members		
Age, years: mean (SD)	xx.x (xx.x)	xx.x (xx.x)
Female gender: *n*/total *n* (%)	x/x (xx.x)	x/x (xx.x)
Years of education: mean (SD)	xx.x (xx.x)	xx.x (xx.x)
Household income, USD: median (IQR)	xx.x (xx.x-xx.x)	xx.x (xx.x-xx.x)
Unemployed: *n*/total *n* (%)	x/x (xx.x)	x/x (xx.x)
Living with care recipient: *n*/total *n* (%)	x/x (xx.x)	x/x (xx.x)
Surrogate decision maker: *n*/total *n* (%)	x/x (xx.x)	x/x(xx.x)
History of anxiety: *n*/total *n* (%)	x/x (xx.x)	x/x (xx.x)
History of depression: *n*/total *n* (%)	x/x (xx.x)	x/x (xx.x)
ICU professionals		
Age, years: mean (SD)	xx.x (xx.x)	xx.x (xx.x)
Female gender: *n*/total *n* (%)	x/x (xx.x)	x/x (xx.x)
Type of ICU professional		
Physician: *n*/total *n* (%)	x/x (xx.x)	x/x (xx.x)
Nurse: *n*/total *n* (%)	x/x (xx.x)	x/x (xx.x)
Nurse technician: *n*/total *n* (%)	x/x (xx.x)	x/x (xx.x)
Physiotherapist: *n*/total *n* (%)	x/x (xx.x)	x/x (xx.x)

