#### Secondary outcomes

We will use the following statistical procedures to evaluate the study secondary outcomes:*Daily hazard of delirium*: The daily hazard of delirium will be analyzed using a joint survival model that accounts for the treatment effect (with adjustment for the cluster effect, period effect, and interaction between cluster and period) on repeated daily indicator of delirium within each patient and terminating event (death or discharge from the ICU) [22]. This outcome will be presented as hazard ratio (HR) and 95% CI.*Any ICU-acquired infections*: The differences in the cumulative incidence of any ICU-acquired infection between the FFVM and RFVM groups will be compared using generalized estimating equations with adjustment for the cluster effect, period effect, and interaction between intervention and period. This outcome will be presented as RR and 95% CI.*Ventilator-free days*: The number of ventilator-free days will be evaluated using the 7-day time horizon. Ventilator-free days will be set to 0 for patients who have died. The differences in the mean ventilator-free days between the FFVM and RFVM groups will be compared using generalized estimating equations with adjustment for the cluster effect, period effect, and interaction between intervention and period. This outcome will be presented as mean difference (MD) and 95% CI.*ICU length of stay*: The differences in the mean ICU length of stay between the FFVM and RFVM groups will be compared using generalized estimating equations with adjustment for the cluster effect, period effect, and interaction between intervention and period. This outcome will be presented as MD and 95% CI.*Hospital mortality*: The differences in hospital mortality rates between the FFVM and RFVM groups will be compared using generalized estimating equations with adjustment for the cluster effect, period effect, and interaction between intervention and period. This outcome will be presented as RR and 95% CI.*Symptoms of anxiety and depression among family members*: The differences in the mean HADS scores for anxiety and depression between the FFVM and RFVM groups will be compared using generalized estimating equations with adjustment for the cluster effect, period effect, and interaction between intervention and period. These outcomes will be presented as MD and 95% CI.*Satisfaction among family members*: The differences in the mean CCFNI satisfaction scores between the FFVM and RFVM groups will be compared using generalized estimating equations with adjustment for the cluster effect, period effect, and interaction between intervention and period. This outcome will be presented as MD and 95% CI.*Prevalence of burnout among the ICU professionals*: Burnout is defined as a cumulative MBI score greater than − 9. The differences in the prevalence of burnout between the FFVM and RFVM groups will be compared using generalized estimating equations with adjustment for the cluster effect and baseline MBI total scores. This outcome will be presented as prevalence ratio and 95% CI.

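### The main HADS anxiety and depression models leave out the relatives' history of anxiety or depression, which is already collected, and so give up a little precision that could be had almost free

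*SAP article*

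**What the plan says.** All places are in the SAP article.

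- **Secondary outcomes, main HADS analysis.** "The differences in the mean HADS scores for anxiety and depression between the FFVM and RFVM groups will be compared using generalized estimating equations", with terms for cluster, period and the intervention-by-period interaction. No characteristic of the relative is in the model.
- **Baseline characteristics, Table 2, family members.** The table has rows for "History of anxiety" and "History of depression", reported by visiting model. It has no row for a baseline HADS score.
- **Secondary outcomes, sensitivity analyses.** The plan states: "We will perform sensitivity analyses to check the consistency of intervention effects on family members and ICU professionals". One of these is "Evaluation of study intervention effects on HADS subscale scores among family members adjusted by previous history of anxiety (for anxiety HADS subscale"), with history of depression used in the same way for the depression subscale.
- **Secondary outcomes, burnout.** Here the main model does carry a baseline value: "generalized estimating equations with adjustment for the cluster effect and baseline MBI total scores".
- **Table 3.** The three family-member secondary outcomes (HADS anxiety, HADS depression, CCFNI satisfaction) are to be reported with 98.3% confidence intervals.

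**The concern.** A relative's history of anxiety or depression can be expected to predict the HADS score on the matching subscale. With no baseline HADS listed, it is the best baseline predictor on the plan's own list. The trial already collects it and already plans the adjusted model, yet the main result comes from the model without it. The SAP gives no reason, and it takes the other course for burnout.

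What is at stake is precision for two secondary outcomes that are judged at a Bonferroni-reduced level, where some power has already been spent. A second question is whether a difference in psychiatric history between the two groups of relatives could distort the main estimate. The working treats the two separately, because the answers differ.

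**Working it through.** **The plan's own figure.** Three family-member comparisons share 0.05: 1 - 0.05/3 = 0.983, which matches the 98.3% in Table 3. The SAP states no figure for HADS variability, prevalence of history or its effect, so everything below rests on labelled assumptions.

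**Inputs**
- Relatives included as of March 2018: 1192 (Discussion and trial status). Assuming an equal split, 596 per model.
- Assumed: prevalence of history p = 15-25%; HADS difference when history is present d = 2-4 points; SD = 4.5 points.

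**1. Precision gained by adjustment.** For a binary covariate, R² = p(1-p)d²/SD², and the standard error is multiplied by √(1-R²).

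| p | d (points) | R² | SE multiplier | SE smaller by |
|---|---|---|---|---|
| 0.15 | 2 | 0.1275 × 4 / 20.25 = 0.025 | 0.987 | 1.3% |
| 0.25 | 3 | 0.1875 × 9 / 20.25 = 0.083 | 0.957 | 4.3% |
| 0.25 | 4 | 0.1875 × 16 / 20.25 = 0.148 | 0.923 | 7.7% |

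These percentages do not depend on the final number of relatives. Over a wider range (p = 10-30%, d = 0.3-1.0 SD), R² runs from 0.8% to 21% and the reduction in SE from 0.4% to 11%. In a central case (p = 20%, d = 0.6 SD), R² = 0.16 × 0.36 = 5.8% and the SE is 2.9% smaller. An effect detectable with 80% power at level 0.05/3 without adjustment (0.187 SD with 596 per model, clustering ignored) would have 82.6% power with it.

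**2. Validity of the unadjusted analysis.** The central case was simulated as a two-period crossover of 40 ICUs with 15 relatives per ICU and period, 4000 runs, no true effect and no selective enrolment. A cluster-level analysis stood in for the planned GEE.
- Mean unadjusted estimate: -0.001 SD, so no bias.
- Type I error: 0.020 unadjusted and 0.020 adjusted, against a nominal 0.0167. Adjustment makes no difference to it.
- Ratio of the spread of the estimates, adjusted to unadjusted: 0.0602/0.0620 = 0.971, which agrees with the 2.9% above after clustering.

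**3. Could an imbalance in history move the result?** The shift equals imbalance × d. An imbalance of 5 percentage points with d = 2 gives 0.1 points; 10 percentage points with d = 4 gives 0.4 points. Without clustering, the SE of the HADS difference is 4.5 × √(2/596) = 0.26 points, so these shifts are about 0.4 to 1.5 SE.

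Chance imbalances of that size are unlikely. The SE of a difference in prevalence is √(2p(1-p)/596), which is 2.1 percentage points at p = 15% and 2.5 at p = 25%. An imbalance of 5-10 points is therefore about 2 (5/2.5) to 4.8 (10/2.07) standard errors. It would need a systematic difference in who enrols.

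**The case against.** **The design is defensible as it stands.** A main model with design terms only, backed by a pre-specified adjusted model, is a legitimate choice. It also follows the plan's pattern for the primary outcome, where adjustment for the PRE-DELIRIC score is a sensitivity analysis. Burnout is the exception, but its covariate is an earlier score on the same instrument, which is usually a stronger predictor than a yes/no history. This stands: the plan contains no error or contradiction here.

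**The gain is small.** This also stands. A reduction of 1-8% in SE will seldom change a conclusion. The argument for the change is that it costs so little.

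**The stronger reading.** A reader might infer that a difference in psychiatric history would be mistaken for an effect of visiting. The document does not support that. Every ICU applies both models, so stable ICU differences cancel. Chance imbalance adds variance that the interval already covers. Table 2 and the planned adjusted analysis would make an imbalance visible. A route to systematic imbalance can be imagined: subjects are recruited after the ICU has started its model, only the flexible model requires relatives to attend a structured meeting, and 1192 relatives are included for 1591 patients (75%). None of this shows that relatives with a psychiatric history enrol differently under the two models. Nor would adjusting for history deal with relatives answering in the knowledge of the visiting model.

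**The change has costs.** The section on missing data has rules for HADS, CCFNI, MBI and PRE-DELIRIC items but none for history, so an adjusted main model could drop relatives, whereas the plan's overall principles keep everyone with a recorded outcome. The SAP also declares no differences from a protocol that is not shown here, and it does not say when history is asked. These points are fair but minor, and a short addition settles them.

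**Conclusion.** The point holds as a minor matter of efficiency. The main HADS analyses omit a collected, clinically matched baseline predictor and use it only as a consistency check. Under the assumed prevalence (15-25%), effect (2-4 points) and SD (4.5), the standard error is about 1-8% smaller with adjustment, and 0.4-11% smaller over the wider range. All these inputs are assumptions.

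The unadjusted analysis remains valid, with no bias and no loss of type I error control relative to the adjusted one unless enrolment of relatives differs systematically between the models. The figures for such an imbalance (0.1-0.4 points) are conditional illustrations only.

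**What to change.** Before the database is locked:

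1. Make the GEE with the planned design terms plus the matching history the main analysis: history of anxiety for the anxiety subscale, history of depression for the depression subscale.
2. Report the GEE without history as the supporting analysis.
3. Add one line on missing history, for example a missing-indicator category or a simple imputation, so that all relatives with a recorded HADS stay in the analysis. State in the same place when history is asked.
4. If the protocol names the unadjusted model as the main one, record the change in the section on differences between protocol and SAP.

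The cost is a reordering of two models already planned, one missing-data rule and possibly one note of departure from the protocol. No new data are needed. The SAP states that it was written without knowledge of the results and before the end of recruitment, so the order can be changed without any appearance of choosing the more favourable model.
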